### Economic evaluation

A cost-utility analysis will be undertaken using the costs, EQ-5D and mortality data from trial. The analysis will take a NHS and Personal Social Services (PSS) perspective, with an additional analysis that incorporates carer QALYs within the incremental cost-effectiveness ratio (ICER). This will be supplemented with decision analytic modelling to estimate lifetime cost-effectiveness for the patient cohort recruited to the trial. Resource use for insertion of the pacing system – theatre time, ward stay and any critical care - will be gathered from theatre and patient administration system (PAS) records. Resource use relating to NIV and other NHS and PSS services will be collected at all follow-up visits. Unit costs for insertion will be based on hospital unit costs. Market prices will be used for the pacing system and its associated costs, with an equivalent annual cost being calculated based on the lifespan of the system based on past experience. NIV costs will be based on business case and contracting information relating to existing NIV services within the participating centres. Other unit costs will be taken from the most recent National Reference Costs, British National Formulary and PSSRU publication ‘Unit costs of health and social care’. The EQ-5D will be completed at baseline and all follow-up visits by patients and the main carer of the patient. QALYs will be estimated using straight line interpolation between data points. Both costs and QALYs will be discounted at 3.5% per annum. Mean incremental costs and QALYs will be combined into an ICER, and sampling uncertainty represented by plots on the cost-effectiveness plane and associated cost-effectiveness acceptability curves (CEACs).

Missing data will be imputed using multiple imputation. An additional analysis will incorporate carer QALYs within the ICER. A decision analytic model will be constructed that will be validated by replicating the results of the trial, and then results extrapolated to conduct a lifetime analysis. Extrapolation will use transition probabilities estimated from a survival analysis based on the 12 month follow-up data from the trial. Probabilistic sensitivity analysis will be undertaken, with further deterministic analyses using SF-6D utilities and including carer utilities. The feasibility of a mixed treatment comparison that includes DiPALS, the study by Bourke et al (2006) and the ongoing Synapse study will be assessed. This will form the basis of an additional cost-effectiveness analysis if a valid comparison can be undertaken. As with the trial based analysis, results will be presented in terms of an ICER and CEACs.

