Diaphragm pacing (DP) is a technique initially developed for the treatment of respiratory muscle weakness in patients with spinal cord injury [10]. In this patient group it has allowed patients to reduce their time on mechanical ventilation or even remove the need for mechanical ventilation [11]. The NeuRX RA/4 System is a four channel percutaneous neuromuscular stimulation system. Intramuscular electrodes are implanted laparoscopically into the abdominal surface of the diaphragm, with leads tunnelled to an exit site on the abdomen. A small external stimulator delivers the stimulus pulses and provides respiratory timing. It is hypothesised that the potential benefits of DP in MND may come from a restoration of the coordination of respiration, lost as a result of upper motor neurone dysfunction, as well as conditioning of diaphragm muscle. In a healthy diaphragm slow twitch type I muscle fibres predominate. Disuse and suppression of the diaphragm activity, due to artificial ventilation, has been demonstrated to lead quickly to atrophy and to a predominance of fast type IIb muscle fibres [12]. The predominant type IIb muscles fibres lead to inefficient uncoordinated diaphragm contractions. In MND a similar process is likely to occur due to disuse (secondary to UMN dysfunction) and suppression of diaphragm activity due to NIV. DP may condition the diaphragm with a conversion back to efficient type I muscle fibres [13].

The anticipated benefits of DP in the MND patient group are: improved survival; improved quality of life; reduction in need for NIV; a less intrusive method of providing respiratory support compared to NIV.

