### Diaphragm pacing

The NeuRx R/A4 device, has been utilized in over 350 patients to date, including two separate investigational device exemption (IDE) trials [14]. There are over 275 patient years of cumulative use of the device with the initial spinal cord injured (SCI) patient utilizing the device continuously for 10 years.

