### Efficacy evidence

A pilot feasibility study of 16 patients with MND implanted with DP demonstrated provisional safety and tolerability data and a decline in forced vital capacity of 0.9% per month following implantation, compared to 2.4% per month before the procedure [13]. One hundred and six MND patients have been implanted with the NeuRX RA/4 Device in a U.S. Food and Drug Administration (FDA) prospective multi-centre trial. The planned primary analysis of this study was the change in rate of decline of FVC between lead-in (3 months) and DP treatment (12 months) phases for patients not using NIV. The full study results have not yet been published. However subgroup data are available following approval of DP for MND patients under the FDA Humanitarian Device Exemption (HDE) Programme [14,15]. For this approval, analysis was performed on a subgroup of patients who met the Humanitarian Use Designation population criteria (HUD #10-0242) i.e., MND patients with a stimulatable diaphragm by voluntary contraction or phrenic nerve conduction studies, and who were symptomatic due to chronic hypoventilation (CH). The physiological criteria for CH were FVC < 50%, or MIP <60cm H_2_0, or PaC0_2_ ≥45mmHg, or nocturnal oximetry demonstrating O_2_ saturations of ≤ 88% for 5 consecutive minutes.

The median overall survival in the HUD subgroup (n = 84) was 56 months from disease onset, 39 months from diagnosis and 19 months from implantation of device. As part of the FDA HUD approval, survival of implanted patients was compared with the standard care NIV alone arm in a published study by Lechtzin et al [16]. DPS HUD group patients with an FVC ≥ 45% but ≤ 65% (n = 43) were selected for the comparison. The DPS HUD group has an improved median survival of 16 months from diagnosis and 9 months from initiation of NIV compared to the Lechtzin NIV group.

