### Safety and tolerability of DP

A total of 350 implantations in Spinal Cord Injured patients and MND patients have taken place [14]. Generally implantation surgery is well tolerated. Detailed safety data has been published on 51 patients with MND who have undergone the implantation procedure (49 in the FDA trial or pilot and 2 compassionate use cases). In the trial/series the FVC at implantation ranged from 45%-89%, whereas the compassionate cases had an FVC of 26% and 28%. All patients were extubated without difficulty and there was no 0 day or 30 day mortality [17].

Within the HDE approval submission safety analysis was performed on the HUD subgroup (n = 86). There were no reports of serious unanticipated adverse device effects and no reports of any serious adverse effects related to the patients’ use of the device following discharge. There were 3 reports of serious adverse events (3.5%) related to implantation. These were pneumothorax (n = 2) requiring intervention and respiratory failure following surgical complications (n = 1) [14]. These were previously recognised risks of laparoscopic procedures.

Discomfort from pacing was reported in 22 patients (26%). This was described as mild in 20 patients and severe in 2 patients. Resolution was achieved in most cases by adjusting the stimulation parameters.

Mild to moderate infection at the percutaneous exit site was reported (n = 9, 9.3%). These were treated with antibiotics. In two cases the subcutaneous wires needed to be repositioned under local anaesthetic.

No serious adverse events occurred as a result of malfunctioning device components. The following malfunctions were reported; anode breaks (n = 18,21%), anode falling out of body (n = 6,7%), external electrode breaks (n = 28, 33%), broken stimulators (n = 6, 7%) and broken stimulator cables (n = 4, 5%) [14]. In practical terms in MND, malfunctioning components resulted in a loss or diminution of conditioning therapy until the malfunction was corrected. Design improvements have subsequently been implemented in an effort to improve reliability and to simplify malfunction resolution.

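### Annuitising the pacing system over its own lifespan leaves part of a single-patient implant charged to nobody if that lifespan exceeds survival; the size depends on a lifespan the protocol does not state

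*Protocol article*

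**What the plan says.** The Economic evaluation section sets a costing rule for the device. The system is valued at market price, and that price is then annualised: "with an equivalent annual cost being calculated based on the lifespan of the system based on past experience". Theatre time, ward stay and critical care for the insertion are costed separately, as resources used. The section also states: "Both costs and QALYs will be discounted at 3.5% per annum". Two results are planned: a cost-utility analysis on the trial data and a decision model that extrapolates to a lifetime.

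Other sections bear on the rule:
- Background: "Intramuscular electrodes are implanted laparoscopically into the abdominal surface of the diaphragm"; their wires leave the body through the abdominal wall. The stimulator is separate: "A small external stimulator delivers the stimulus pulses and provides respiratory timing".
- Diaphragm pacing: the longest experience is in spinal cord injury, "with the initial spinal cord injured (SCI) patient utilizing the device continuously for 10 years".
- Efficacy evidence: median survival in the MND subgroup was "39 months from diagnosis and 19 months from implantation of device".
- Safety and tolerability of DP: external electrode breaks in 33% and broken stimulators in 7% of that subgroup, with design improvements since.

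The article gives no lifespan in years and no device price. It does not say whether any part is reissued to another patient, or whether an unexpired balance is charged at death.

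**The concern.** An equivalent annual cost recovers the purchase price only if somebody uses, and is charged for, the item throughout the annuity period. That suits equipment passed from patient to patient. Electrodes placed in one patient's diaphragm are paid for in full at the operation and have no later user. If the annuity period is the durability of the device and the patient dies sooner, the remaining annual charges are never made.

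The device price falls on the DP arm only. Any shortfall therefore lowers incremental cost one for one, raises DP's net benefit at every threshold, and lowers the incremental cost-effectiveness ratio (ICER) when the QALY gain is positive. The acceptability curves move the same way. The planned further analyses (probabilistic sensitivity analysis, SF-6D utilities, carer utilities) are not directed at this rule.

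**Working it through.** The plan states no device cost that could be reproduced, so results are given as shares of the price.

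**Inputs**
- Rate r = 3.5% a year. This is the stated discount rate; using it as the annuity rate is an assumption.
- Lifespan L = 3, 5 and 10 years. All are assumptions; 10 years matches the longest single user reported.
- Survival on DP, assumed exponential, in two versions: 70% at one year (Sample size section) and a median of 19 months (Efficacy evidence section). As a check on the first, ln 0.70 / ln 0.45 = 0.447, which agrees with the planned hazard ratio of 0.45. Time from randomisation is treated as time from implantation.
- Hazards per year: λ = -ln 0.70 = 0.357, mean survival 1/λ = 2.80 years; or λ = ln 2 / (19/12) = 0.438, mean 2.28 years.

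**Step 1. One full year's charge.** Share of price = r / (1 - 1.035^-L).
- L = 3: 0.357
- L = 5: 1/4.515 = 0.221
- L = 10: 1/8.317 = 0.120

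**Step 2. Expected charge while alive, discounted.** With d = ln 1.035 = 0.0344, k = λ + d and continuous annuity factor a = (1 - 1.035^-L)/d, the lifetime share is 1/(k·a) and the 12-month share is (1 - e^-k)/(k·a). Example for 70% at one year and L = 5: k = 0.391, a = 4.59, lifetime share = 1/(0.391 × 4.59) = 0.56.

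| Lifespan L | Lifetime share: 70% at 1 year | Lifetime share: median 19 months | 12-month share: 70% at 1 year | 12-month share: median 19 months |
|---|---|---|---|---|
| Mean survival (2.80 or 2.28 years) | 0.96 | 0.96 | 0.31 | 0.36 |
| 3 years | 0.90 | 0.74 | 0.29 | 0.28 |
| 5 years | 0.56 | 0.46 | 0.18 | 0.17 |
| 10 years | 0.30 | 0.25 | 0.10 | 0.09 |

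Charging in full at implantation would give 1.00. The lifetime columns let the charge run for as long as the patient lives. If it stops at the end of the lifespan, the shares fall to 0.56-0.62 (3 years), 0.42-0.48 (5 years) and 0.25-0.30 (10 years).

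**Step 3. The part of the 12-month shortfall due to deaths.** With 70% alive at one year, mean time alive in the year is (1 - 0.70)/0.357 = 0.841 years. Those who die therefore live on average (0.841 - 0.70)/0.30 = 0.47 years. Ignoring discounting within the year, they are charged 0.47 × 0.357 = 0.17, 0.47 × 0.221 = 0.10 or 0.47 × 0.120 = 0.06 of the price. Their unpaid balance per implanted patient is 0.30 × 0.83 = 0.25, 0.30 × 0.90 = 0.27 or 0.30 × 0.94 = 0.28. The whole 12-month shortfall is 0.71, 0.82 or 0.90, so roughly a third of it belongs to patients with no later use of the device. The rest is deferral for survivors.

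**The case against.** The lifespan is not stated, and everything turns on it. The ten-year figure comes from one spinal cord injury patient. The article's own experience is over 275 patient-years in over 350 patients, about 0.8 years each; this is censored and not a lifespan estimate, but it shows how extreme ten years is. Frequent failure of external parts could also point to a short lifespan. If lifespan means duration of use in MND, the lifetime shortfall almost disappears. This objection stands and fixes the lower end of the range. It does not remove the point: the natural meaning of a system's lifespan is durability, and the article does not choose the other meaning.

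A reader might infer that the whole device cost is understated 2- to 10-fold in both analyses and that the ICER is certainly biased towards adoption. The documents do not support that:
- The 10-fold end is the 12-month share at a ten-year lifespan. It counts as lost the cost deferred for the planned 70% still alive, who have benefit to come.
- The stimulator is external and may be reissued. No price split is given, so the shortfall cannot be applied with confidence to the whole system.
- Insertion costs are counted separately, so the effect on total incremental cost is unknown.

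Full price within 12 months also has a cost of its own: it sets a whole device against at most one year of benefit.

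Finally, a condensed article may leave component costing to a fuller plan. That excuses the missing number of years. It does not excuse the stated rule, which applies the annual cost to the pacing system without separating single-patient parts.

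**Conclusion.** The concern holds conditionally. As written, the rule undercharges single-patient components whenever the chosen lifespan exceeds survival after implantation and the balance is not charged at death. In the lifetime model, recovery is about 74-90%, 46-56% and 25-30% of the annuitised price at assumed lifespans of 3, 5 and 10 years, and about 96% if lifespan means mean duration of use in MND. The understatement thus runs from negligible (1/0.96 = 1.04) to about 4-fold (1/0.25), and on the annuitised price only. In the 12-month analysis the clear undercharge is the balance for patients who die within the year, about a quarter of the price per implanted patient under the planned 70% survival.

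These figures rest on exponential survival, a 3.5% annuity rate, assumed lifespans and no reissue of parts. The ICER and acceptability curves are affected, in DP's favour; the primary survival analysis and the sample size are not.

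**What to change.** Replace the device-cost sentence in the economic plan so that:
- **Lifetime model:** implanted and other single-patient components are charged at full market price at implantation, plus replacement parts actually used. An equivalent annual cost is kept only for components shown to be reissued to other patients, with the lifespan stated in years and its source given.
- **12-month analysis:** at least the unexpired balance is charged when a patient dies, and results are reported with both full-price and annuitised device cost, so that the effect of the choice is visible.

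This takes a sentence or two, a component price list and information on which parts are reissued; no new patient data are needed. The downside is that the stated cost of DP becomes less favourable, and the full-price 12-month result must be read as a whole device set against at most one year of benefit.

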### Data collection

Once participants have been enrolled and allocated their treatment the data collection process starts (Table 1). Data collection occurs at baseline, 2, 3, 6, 9 and 12 months for both groups. Additionally the DP group will undergo data collection at the time of surgery and 1 week following surgery. The subgroup of 12 participants and carers who will be undertaking the qualitative sub study will also undergo interviews at 1 and 6 months post implantation.

**Table 1 T1:** Data collection

**Data collection tool**	**Time point of study**	**When collected/given to patient**	**By who**	**Purpose**
Informed consent form	Recruitment	In clinic, face to face	Neurology or respiratory consultant	Ensure participants have been consented appropriately
Screening and eligibility assessment form	Recruitment/Screening	In clinic	Neurology or respiratory consultant or research nurse	Ensure protocol violations or deviations are avoided. Include ECG, blood gases, blood test, FVC and phrenic nerve evaluation tests
ALSFRSr	Screening	As above	As above	Allows minimisation on bulbar function
Survival	1 week, 2, 3, 6, 9, 12 months, then finally at last follow up for last patient	In clinic, telephone	Research nurse	Primary outcome measure
*EQ5D questionnaire (patient and carer)	Screening, 2, 3, 6, 9 and 12 months	In clinic or over the phone	Neurology or respiratory consultant or research nurse	QALYs, secondary outcome measure
SF36	Screening, 2, 3, 6 and 12 months	As above	As above	Generic quality of life, secondary outcome measure
Sleep Apnoea Quality of Life (SAQLI)	Screening, 2, 3, 6 and 12 months	As above	As above	Respiratory specific quality of life, secondary outcome measure
*Caregiver Burden Inventory questionnaire	Screening, 2, 3, 6 and 12 months	As above	As above	Secondary outcome measure
Side effects/ adverse event/concomitant medications and devices forms	All time points as required	As above	As above	AE/SAEs
Healthcare resource use	2, 3, 6, 9 and 12 months	As above	As above	Economic, secondary outcome measure
Patient Diary incorporating:	1 week, 2, 3, 6, 9 and 12 months	In clinic, at hospital or at home	Neurology or respiratory consultant and Patient and Carer	Main outcome Record DP and NIV use
* NIV use				
* DP use and				
* DP Parameters setting				
NIV use	Screening	As above	As above	Main outcome
Medical history and examination on CRF	Screening and 12 months	In clinic	Neurology or respiratory consultant	Eligibility for trial, safety

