### Statistics

#### Sample size

The sample size calculation is based on log-rank test, using Simpson’s rule as implemented in Stata version 11.1 [23] to allow for the unequal length of follow-up [24]. The study duration comprises an 18-month recruitment period and a 12-month follow-up period, giving a maximum follow-up of 30 months and a minimum of 12 months. Assuming control group survival proportions of 45%, 20% and 10% at the minimum, average and maximum follow-up times respectively, a hazard ratio of 0.45 and an additional 10% loss-to-follow-up, a total of 108 patients (54 per group) are needed to ensure a power of 85% using a two-sided type I error of 5%. The control group figures are conservative estimates based on the sole randomised controlled trial of NIV, which is now considered standard care in the UK. The FDA study of DP in ALS/MND has estimated a one year survival of 86% after study entry for patients using DP and NIV (personal communication). We have estimated the sample size on a conservative (but clinically important) 1-year difference in survival of 45% versus 70%, which produces the estimated hazard ratio of 0.45. It is anticipated that we will have complete survival data on all subjects recruited, based on previous experience in MND trials. With regard to quality of life data we anticipate a low level of missing data due to loss to follow up. We have reviewed the patients who were initiated on NIV in the year up to Jun 2009 at the study sites and we have maintained contact with 100% of those patients surviving at 12 months. The appointment of a research nurse at each study site will enable home visits if necessary to collect the quality of life data. We have however allowed for a 10% loss to follow up in the sample size/power calculation.

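### The lifetime economic model takes its survival input from 12-month data, although survival is followed for 12 to 30 months; about a third of expected deaths would not inform it

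*Protocol article*

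**What the plan says.** The Economic evaluation section plans a within-trial cost-utility analysis, supplemented by a lifetime decision model for the recruited cohort. It fixes the source of the model's survival input: "Extrapolation will use transition probabilities estimated from a survival analysis based on the 12 month follow-up data from the trial". It also says "A decision analytic model will be constructed that will be validated by replicating the results of the trial".

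Elsewhere the article plans longer survival follow-up:

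- Sample size: the section describes the trial's timetable as "giving a maximum follow-up of 30 months and a minimum of 12 months" for individual patients.
- Data collection, Table 1, Survival row: "1 week, 2, 3, 6, 9, 12 months, then finally at last follow up for last patient".
- Data analysis: the primary outcome is time from randomisation to death, with no cut at 12 months.

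In Table 1, EQ-5D, SF-36, resource use and the NIV/DP diary all end at 12 months. Survival is the outcome that has a later check.

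**The concern.** A lifetime cost per QALY depends heavily on survival after the first year. The plan expects about 70% of the DP arm to be alive at 12 months, so much of that arm's remaining life, and the QALYs and costs attached to it, falls after the model's data stop. For months 12 to 30 the trial will have observed deaths in these same patients, but the model as described would predict that period.

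Two things are at stake. The survival input rests on fewer deaths than are available, most noticeably in the DP arm. And whether a DP effect persists, fades or grows after month 12 would not be estimated in the model, although the trial gathers direct evidence on it. The article gives no reason for limiting the mortality input to 12 months.

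**Working it through.** **Inputs, all from Sample size.** Control survival: "Assuming control group survival proportions of 45%, 20% and 10% at the minimum, average and maximum follow-up times respectively", that is 12, 21 and 30 months. Effect and loss: "a hazard ratio of 0.45 and an additional 10% loss-to-follow-up". Size: 54 per group, 85% power, two-sided 5%, log-rank test with Simpson's rule.

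**Step 1: reproduce the plan's sample size.**

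- Probability of death over follow-up by Simpson's rule: 1 − (S12 + 4·S21 + S30)/6.
- Control: 1 − (0.45 + 4×0.20 + 0.10)/6 = 0.775.
- DP, with each survival raised to the power 0.45 (0.698, 0.485, 0.355): 1 − (0.698 + 4×0.485 + 0.355)/6 = 0.501.
- Mean of the two arms: 0.638.
- Events by the Freedman formula: (1.960 + 1.036)² × (1.45/0.55)² = 62.4.
- Patients: 62.4/0.638 = 97.8, and 97.8/0.90 = 108.6, against the stated 108.

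The inputs therefore reproduce the plan's figure closely, and the same survival curves can be used to count deaths.

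**Step 2: expected deaths, no loss.**

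| Arm | By 12 months | By study end | Not used | Share |
|---|---|---|---|---|
| Control | 54 × 0.550 = 29.7 | 54 × 0.775 = 41.9 | 12.2 | 29% |
| DP | 54 × (1 − 0.698) = 16.3 | 54 × 0.501 = 27.1 | 10.8 | 40% |
| Both | 46.0 | 68.9 | 22.9 | 33% |

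**Step 3: sensitivity of the share.**

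- With the 10% loss applied, the totals are 41.4 and 62.0. The share is still 33%.
- With piecewise-exponential curves and uniform recruitment instead of Simpson's rule, the mean death probability is 0.637 and the share is 33%.
- With no DP effect (hazard ratio 1), both arms follow the control curve: 108 × 0.55 = 59.4 against 108 × 0.775 = 83.7, so 24.3 deaths or 29%.

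The loss of roughly a third does not depend on which survival distribution is later fitted.

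**Step 4: precision, as an illustration only.** If a constant hazard were fitted to the DP arm, the approximate 95% factor either side of the estimate would be exp(1.96/√16.3) = 1.63 from 12-month data and exp(1.96/√27.1) = 1.46 from all data. The article does not say that a constant hazard will be used.

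**The case against.** Several objections have force.

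**No distribution is named.** One could carry the first-year control hazard forward, −ln(0.45)/12 = 0.0665 per month, obtain 24.7% and 13.6% alive at 21 and 30 months against the planned 20% and 10%, and infer that the model would overstate survival by 5 and 4 points. The article does not support that inference, because it never specifies a constant hazard. The choice of distribution is detail that an article may leave to the fuller analysis plan.

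**The planning figures do not show a changing hazard.** Converted to monthly hazards they give 0.067, 0.090 and 0.077, which a reader might take as an assumed later rise. They are three rounded proportions chosen for a sample-size calculation. A single hazard of 0.0703 per month gives 43.0%, 22.8% and 12.1%, within 3 points of each. The sampling error of 45% in 54 patients is √(0.45×0.55/54) = 6.8 points.

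**The validation step is legitimate.** A reader might say that replicating the trial is no validation because the model was fitted to the trial. But the trial's results include survival beyond 12 months, so this internal check could cover months 12 to 30. The article does not say whether it will.

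**There is a visible reason for 12 months.** Utilities, costs and diary data end there, and transition probabilities may include states other than death. This explains a 12-month basis for those inputs. It does not explain one for mortality.

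**The phrase has a second reading.** Sample size also uses a 12-month follow-up period for the phase after recruitment closes, which would admit the longer data. Secondary research objectives uses it for the per-patient window in which endpoints are compared, and that is the more natural reading here. If the other was meant, the sentence still needs clarifying.

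**The reach is limited.** All deaths still count in the primary analysis. The model supplements the within-trial analysis, and probabilistic sensitivity analysis is planned.

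**Conclusion.** The point holds as one about unused information in the lifetime model. On the plain reading, about 23 of 69 expected deaths (33%, and about 40% in the DP arm) would not inform the extrapolation, and months 12 to 30 would be predicted where they are observed. This lowers precision and leaves any later DP effect outside the model's evidence.

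The count rests on the plan's control survival figures, proportional hazards at 0.45, even recruitment over 18 months and no loss. The share is unchanged with 10% loss and is 29% if DP has no effect.

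No claim about bias follows: its direction and size depend on a distribution that is not stated. The consequence is moderate and confined to the supplementary lifetime cost-effectiveness result.

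**What to change.** Change the one sentence in Economic evaluation so that:

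- mortality transition probabilities are estimated from all survival follow-up to the final survival check, with extrapolation only beyond that;
- EQ-5D, resource use and any non-death states keep their 12-month basis;
- the fit to 12-month data is reported as a sensitivity analysis and compared with observed survival from 12 to 30 months.

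If the longer data were always intended, say so explicitly. The cost is one reworded sentence and one additional model fit. No new data collection is needed, because the survival data are already gathered for the primary outcome.
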